### Intervention

During the trial period, participants in the treatment group will be given BDJ exercise combined with Calcium carbonate and D3, and in the control group will be only given Calcium carbonate and D3. The intervention period will last 24 weeks. The requirements for the BDJ exercise will be as follows.Preparatory stage (the first 2 weeks, mastering movements stage)Participants need to be organized to practice BDJ exercise for 3 times a week. The researchers will hire professional coaches to guide and correct the movements. During rest time, research assistants will distribute free videos to practice by themselves at home.Conventional stage (the last 22 weeks, regular exercise stage)The participants need to exercise 3 times a week, 30 to 60 min each time, and the amount of exercise may be appropriate as long as the participants do not experience fatigue. The research assistants will lead exercise once a month, and the rest time will be practiced by themselves. The researchers will give monthly follow-up calls or home visits to record the completion and adjust the exercise frequency according to the actual conditions. During the trial period, the researchers will instruct the participants to avoid other physical activities as much as possible, for example, swimming. If there are associated exercises, the research assistant needs to record details.We will recommend the participants form a small team to exercise together with their familiar people, and distribute free brochures, BDJ exercise teaching videos and special lectures about OP at different periods, so as to maximize enthusiasm and compliance, which can ensure the study completion to the greatest extent.

### Outcome assessment

Variables in this study included basic information, clinical characteristics, adverse events, primary and secondary outcomes. We will collect basic information and clinical characteristics at baseline (1 week before randomization). Primary and secondary outcomes will be measured at baseline and after the 6th month of treatment (6 months after enrollment). In addition, follow-up assessments will be conducted at 6th month after the end of treatment (12 months after enrollment). All primary and secondary outcomes will be assessed by professionally qualified doctors who will be unaware of assigned outcomes.Basic information and clinical characteristicsResearch assistants will use the Case Report Form (CRF) designed for this study to collect basic information and clinical characteristics, including gender, age, education, height, weight, waist circumference, hip circumference, co-morbid history, personal life history and medication use. Body mass index (BMI) was calculated from height and body mass, and waist-to-hip ratio was calculated from waist circumference and hip circumference.Primary outcomesPain induced OP is measured using the visual analogue scale (VAS, 0–10 points). 0 point represents no pain, 1–3 points are mild pain, 4–6 points represent moderate pain, although the pain is strong but still tolerable, 7–10 points represent severe pain, which gradually reaches difficult degree of tolerance.Balance ability is measured using the Berg balance scale (BBS, 0–56 points). The higher the score, the better the balance ability. At the same time, the risk of falling can be assessed according to the results: BBS < 40 points means at risk of falling.Secondary outcomesBone mineral density (BMD) is measured using DXA. Fixed professionals are responsible for the verification and measurement of the machine, and the inspection parts mainly include lumbar vertebrae (L1-L4) and bilateral hips.Laboratory tests (blood serum) are measured with Luminex Assay. With reference to the Recommended Experiments for Biochemical Indicators of Bone Metabolism (2020 Expert Consensus, China) [20], the preliminary research results, and the literature survey, The serological indicators include Type I Procollagen N-terminal Propeptide (P1NP), β-collagen Degradation Product (β-CTX), Myostatin (MSTN), Fibroblast Growth Factor-23 (FGF-23), and Neuropeptide Y (NPY). Qualified researchers will draw 5 ml of venous blood from the participants in the morning on an empty stomach, and complete the aliquots within 30 min.Fall risk is measured with the timed “up and go” (TUG) test and morse fall scale (MFS). Research assistants need to record the time, the participant's gait, and the falling risk according to the following criteria: 1 point is normal, 2 points are very slightly abnormal, 3 points are mildly abnormal, 4 points are moderate abnormality, 5 points are severe abnormality. The MFS was developed by [name] in 1989. The content of the scale evaluation involves the history of falls in the past 3 months, gait, cognition, etc. The total score is 125 points, and the higher the score, the greater the risk of falling. A score greater than 45 is considered high risk of falling, 25 to 45 is considered medium risk, and less than 25 is considered low risk.Lower extremity muscle strength is measured with five-times sit-to-stand test (FTSST). The assistants need to record the total time spent. At last, the test was performed 3 times and the final average was taken.

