### Randomization

Participants who meet the inclusion and exclusion criteria will be randomly divided into the control group and the treatment group, with 80 patients in each group. Due to the peculiarities of BDJ exercise itself, we could not blind participants or trainers, but outcome assessors and statisticians will be blind. The research will entrust a professional data management department to generate random numbers system (http://112.126.58.121:8082/bdj) and monitor trial quality. According to the group designated by the random number, research assistants accurately record the participants' random number, group, and intervention.

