
### Safety measurements

Research assistants will monitor participants for adverse events during the treatment. Research assistants guide the preparation and relaxation exercises before and after the practice to prevent the elderly from being injured. During the trial period, the BDJ exercise should be stopped if serious complications, other diseases, or adverse reactions occur. Meanwhile, corresponding treatment measures should be taken. Any adverse events that occur will be reported immediately and in detail to the research center that will assess the causal relationship and severity associated with the intervention. Serious adverse events will be reported to the ethics committee to decide the next steps.

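### Assessor blinding is not secured for TUG and FTSST: both are given to research assistants, a role that also records allocation and leads the Baduanjin sessions

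*Protocol article*

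**What the plan says.** All references are to the protocol article.

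- **Who is blind.** The Randomization section says "we could not blind participants or trainers, but outcome assessors and statisticians will be blind".
- **Who assesses.** Outcome assessment makes a statement covering every outcome: "All primary and secondary outcomes will be assessed by professionally qualified doctors who will be unaware of assigned outcomes". The closing words presumably mean the assigned group.
- **TUG.** Under the secondary outcomes of the same section, "Research assistants need to record the time", together with gait and a five-level grade running from normal to severe abnormality.
- **FTSST.** "The assistants need to record the total time spent", with the result averaged over three performances. No grade is attached to this test.
- **What else research assistants do.** Under Randomization, "research assistants accurately record the participants' random number, group, and intervention". Under Intervention, "The research assistants will lead exercise once a month" during the last 22 weeks. Under Safety measurements, "Research assistants guide the preparation and relaxation exercises before and after the practice".
- **Pain.** The VAS (0–10) is one of the two primary outcomes. The article does not say who marks it.

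**The concern.** The section says that unaware doctors assess every outcome and then hands two of the outcomes to a different staff role. That role's other duties bring it into contact with the allocation, both on paper and in the exercise room. Both statements about who assesses cannot hold as written.

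At stake is detection bias. Someone who knows the group and has led the exercise may start or stop a stopwatch a little differently, encourage differently, or grade gait more kindly. The TUG grade is the most exposed because it is a judgement. TUG is also one of the two fall-risk measures, and the article hopes to support recommending Baduanjin to prevent falls, so a biased TUG result would bear on the intended message even though it is a secondary outcome.

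**Working it through.** The article gives no figure to reproduce. The check sets the sections side by side by role.

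**Step 1: which role knows the allocation?** Research assistants write down the group and intervention (Randomization), lead the monthly sessions (Intervention), and guide preparation and relaxation around practice (Safety measurements). As a role they are therefore aware of allocation. The article itself concedes that trainers cannot be blinded.

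**Step 2: which role measures each outcome?**

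| Outcome | Measured by, in the specific text | Consistent with blinded doctors? |
|---|---|---|
| TUG: time, gait, 1–5 grade | Research assistants | No |
| FTSST: time only | The assistants | No |
| BBS (primary), MFS | No clear statement other than the general one | Not clearly contradicted |
| BMD, laboratory tests | Professional or qualified staff | Blinding not clearly contradicted |
| Pain VAS (primary) | Not stated; by its nature a self-rating | Assessor blinding cannot protect it |

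**Step 3: is there a separation of duties?** No section distinguishes assistants who assess from assistants who record allocation or attend sessions.

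**Step 4: what could a scoring shift do?** This is an illustration. The inputs are 64 per arm (the Sample size section's VAS-based figure before dropout), a two-sided 5% test with critical value 1.96, no true effect, and an assumed systematic shift of d standard deviations in favour of Baduanjin. The article gives no value for d.

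- Standardised shift: z = d / √(2/64) = d / 0.1768
- False-positive probability: Φ(z − 1.96) + Φ(−z − 1.96)

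| Assumed d | z | Probability |
|---|---|---|
| 0 | 0 | 0.025 + 0.025 = 0.050 |
| 0.10 | 0.566 | 0.0816 + 0.0058 = 0.087 |
| 0.25 | 1.414 | 0.2926 + 0.0004 = 0.293 |
| 0.40 | 2.263 | 0.6190 + 0.0000 = 0.619 |

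The test here is a plain two-sample z-test. The article plans a baseline-adjusted GEE with a group-by-time interaction, so these figures show how sensitive the error rate is to a shift. They do not predict this trial's error rate.

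**The case against.** **Different people may do the two jobs.** Research assistant is a broad label in this article. It covers consent, recording of group, monthly sessions, case report forms, adverse events and data entry, in a trial recruiting across Beijing, Tianjin and Shaanxi. The article says outright that assessors will be blind, and individual delegation is something a full protocol may set out. This stands in part. The article does not show that the same individuals deliver the exercise and hold the stopwatch, so a reader who concludes that the blinding is false for these tests goes too far. What remains is that the article promises doctors for all outcomes, names assistants for two, and offers no separation of duties. Condensing a longer document does not explain a contradiction within one section.

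**Pain VAS.** A reader might infer that the VAS is a second contradiction, or that a pain result will be presented as blinded evidence. The documents do not support either. The article states that participants could not be blinded, self-reported pain is an unavoidable limit of an exercise trial, and no section says how a VAS result will be described. The statement covering all outcomes is merely loose on this point.

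**How much assistants deliver.** Hired coaches teach and correct movements in the first two weeks. After that, assistants lead once a month and the rest is self-practice. Monthly follow-up calls or visits belong to the researchers, not expressly to the research assistants. The exposure is real but should not be described as full delivery of the intervention.

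**Size.** The shift is invented, the 64 per arm was derived for VAS, and the test is simpler than the planned one. All of this stands, so the calculation is an illustration only.

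**Conclusion.** The concern holds in a limited form. As written, the article contradicts itself on who measures TUG and FTSST, and it assigns them to a role whose other duties reveal the allocation. The stated assessor blinding is therefore not secured for these two secondary outcomes. The subjective TUG grade is the most vulnerable part; for FTSST only the timing is exposed.

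Blinded assessment of BBS is not contradicted anywhere. VAS calls for a clarifying sentence and nothing more.

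The conclusion rests on reading research assistant as one role, because the article draws no line within it. It does not rest on any assumed size of bias: that size is unknown, and the 29% figure follows only if a 0.25 SD shift is supposed. Since the conflict touches secondary outcomes and is easily corrected, it should be put right but does not threaten the trial.

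**What to change.** 1. Have the blinded doctors already named under Outcome assessment measure and grade TUG and time FTSST. Alternatively, restrict these tasks to assistants who neither record allocation nor take part in Baduanjin sessions, and say so.
2. Reconcile Randomization, Intervention, Outcome assessment and Safety measurements so that each outcome has one named assessor role and each role has one blinding status. Correct the wording about assigned outcomes to refer to the assigned group.
3. Qualify the sentence on blinded assessment of all outcomes: pain VAS is the rating of participants who know their group, so assessor blinding cannot protect it.

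The first option uses doctors the article already assigns to outcome assessment. The cost is a little more assessor time at each visit, or some rostering of assistants under the alternative, plus wording. Sample size, visit schedule and analysis are unaffected.

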
### Safety measurements

Research assistants will monitor participants for adverse events during the treatment. Research assistants guide the preparation and relaxation exercises before and after the practice to prevent the elderly from being injured. During the trial period, the BDJ exercise should be stopped if serious complications, other diseases, or adverse reactions occur. Meanwhile, corresponding treatment measures should be taken. Any adverse events that occur will be reported immediately and in detail to the research center that will assess the causal relationship and severity associated with the intervention. Serious adverse events will be reported to the ethics committee to decide the next steps.

### Sample size

According to the existing results combined with expert experience [21, 22], we assume α = 0.05 and β = 0.10 based on an allocation ratio of 1:1, then the sample size is 64 cases respectively in the two groups, totaling 128 cases according to VAS. Considering the 20% dropout rate, a total sample size of 160 cases is required. Then, we also calculated the sample size to be 146 cases according to BBS. Finally, we set the sample size of this study to 160 cases.

### Data collection and management

Data will be recorded on CRF, which will be reviewed and validated by statistical experts for final analysis. First, it is converted into electronic data through the EpiData (EpiData Association, Denmark) by two independent research assistants after the consistency of data is checked in CRF. When all information is finally confirmed, the electronic database will eventually be locked.

### Statistical analysis

All statistical analyses were performed using SPSS 25.0 and Python 3.11. Statistical significance was set at a P value less than 0.05. Continuous variables that conform to a normal distribution are represented by the mean and standard deviation, and variables that do not conform to a normal distribution are represented by the median and interquartile range. Categorical variables will be described as frequencies or percentages. Missing data will be filled in using multiple imputation.

To account for correlation among repeated measurements, intervention effects on the primary and secondary outcomes were examined by generalized estimating equations (GEE) with baseline measurement as the covariates. The group-by-time interaction, which indicated the difference for a given outcome between interventions over time, was considered our primary measure of intervention effects.

Adverse effects will be analyzed using the χ^2^ test or Fisher's test. If it cannot run a normal analysis, we will choose descriptive analysis for presentation.

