**Methods:**

In the prospective randomized controlled trial, 160 participants will be recruited and randomized to the treatment group (BDJ exercise combined with Calcium carbonate and D3) or the control group (Calcium carbonate and D3) at 1:1 ratio. Participants in the treatment group will receive 24-week BDJ exercise for 30–60 min, 3 times a week, along with Calcium carbonate and D3 at each day, while participants in the control group will receive Calcium carbonate and D3 only. All outcome indicators will be measured at baseline, after the 6th month of treatment and 6th month after the end of treatment. The primary outcomes include pain and balance ability, as measured by the visual analogue scale (VAS) and Berg balance scale (BBS). The secondary outcomes will primarily include bone mineral density (BMD), laboratory tests (including P1NP, β-CTX, MSTN, FDF-23, NPY), the timed “up and go” (TUG) test, the morse fall scale (MFS), the five-times sit-to-stand test (FTSST).

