However, there are several limitations in our study. Firstly, there are no guidelines to reconsider the most appropriate type, frequency, intensity and duration of physical activity in patients with OP to prevent bone loss and fracture from a clinical perspective [6]. Therefore, we can only explore the optimal frequency and intensity of BDJ exercise based on current experience and experts’ recommendation. Secondly, how to coordinate breathing, posture and thinking is the key when practicing BDJ exercise. It requires the mind, body and breathing to participate in the training at the same time, in order to achieve the coordination and unity of the whole body, as well as the desired results to the greatest extent. Moreover, the effect may not be ideal, if it is not practiced correctly and if the practitioner does not have a proper grasp of the inherent nature. Therefore, we try to avoid it as much as possible by resorting to more guidance and explanation from professionals, but it is undeniable that it does exist.

The study will investigate the effectiveness of BDJ exercise on improving pain and balance performance in patients with OP. The results hopefully confirm that BDJ exercise, as a non-drug intervention, should be recommended for patients with OP to prevent bone loss, falls and fractures. The ultimate goal is to translate our findings into concrete recommendations that can be used in clinical practice. In addition, the findings may provide a basis for further exploration of the mechanism of BDJ exercise.

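### Two primary outcomes share one unadjusted 0.05 threshold, with no rule on whether one or both must succeed and no fixed primary visit or contrast

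*Protocol article*

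**What the plan says.** The Abstract (Methods) names two primary outcomes: "The primary outcomes include pain and balance ability, as measured by the visual analogue scale (VAS) and Berg balance scale (BBS"). The Outcome assessment section repeats this and sets two post-baseline visits: "Primary and secondary outcomes will be measured at baseline and after the 6th month of treatment (6 months after enrollment"), and "follow-up assessments will be conducted at 6th month after the end of treatment (12 months after enrollment"). Neither visit is named as primary.

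The Sample size section gives one set of design values: "we assume α = 0.05 and β = 0.10 based on an allocation ratio of 1:1". For pain it states that "the sample size is 64 cases respectively in the two groups, totaling 128 cases according to VAS", which a 20% dropout allowance raises to 160. A separate calculation for BBS gives 146, without saying whether dropout is included. No effect size, standard deviation or sidedness is given.

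The Statistical analysis section sets the threshold ("Statistical significance was set at a P value less than 0.05") and uses the same GEE, with baseline as covariate, for primary and secondary outcomes. It calls the group-by-time interaction for each outcome the primary measure of effect. Nowhere does the article order the two outcomes, divide alpha or require both.

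The Discussion hopes to confirm that the exercise "should be recommended for patients with OP to prevent bone loss, falls and fractures".

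**The concern.** With two primary outcomes, an alpha of 0.05 and a power of 90% have no trial-level meaning until the success rule is known. If either outcome suffices, there are two chances of a false positive. If both must succeed, there are two chances to miss. The article permits both readings, so the choice could be made after the results are seen.

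The named measure does not settle which test counts. If baseline enters only as a covariate, the remaining time levels are 6 and 12 months. The interaction then asks whether the group difference changes between those visits, not whether there is a benefit. If baseline is also kept as a time level, each outcome has two interaction coefficients. On either coding, the contrast behind a claim of benefit on pain or balance has not been fixed.

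**Working it through.** **Inputs.** Two primary outcomes (Abstract; Outcome assessment). Alpha 0.05, power 0.90, 1:1 allocation, 64 per arm for VAS, 20% dropout, 146 for BBS (Sample size). One threshold of 0.05 (Statistical analysis). Assumptions of this check: two-sided tests, normal approximation, and the correlation r between the two test statistics, which the article does not give.

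**The plan's own figure.** 128 / (1 − 0.20) = 160, as stated. The 64 per arm cannot be rebuilt without an effect size. It implies a standardized difference of (1.960 + 1.282) × √(2/64) = 0.573.

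**Reading A: either outcome suffices.** For independent tests, the chance of at least one false positive is 1 − 0.95² = 0.0975. For correlated tests, from a bivariate normal simulation with 2,000,000 draws:

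| r | Chance of at least one false positive |
|---|---|
| 0 | 9.75% (formula) |
| 0.3 | 9.5% |
| 0.5 | 9.1% |
| 0.7 | 8.4% |

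**Reading B: both required.** A false trial-level success needs a false rejection on at least one outcome with no true effect, and that particular test has level 0.05. The error is therefore at most 5%. Joint power with 90% for each outcome is 0.90 × 0.90 = 0.81 if independent, 0.822 at r = 0.3 and 0.832 at r = 0.5. It reaches 0.90 only at perfect correlation.

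**How the BBS figure of 146 affects this.** The 90% for BBS is itself uncertain at 64 evaluable per arm.
- If 146 includes dropout: 146 × 0.80 = 116.8 evaluable, or 58.4 per arm. The implied difference is 0.600 and BBS power at 64 per arm is 92.4%. Joint power if independent is 0.90 × 0.924 = 0.832.
- If it does not: 146 / 0.80 = 182.5, so 183, which exceeds 160. With 73 per arm the implied difference is 0.537 and BBS power at 64 per arm is 85.9%. Joint power if independent is 0.90 × 0.859 = 0.773.

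**Cost of alpha control for VAS.** At level 0.025 with 64 per arm, the standardized effect is 0.573 × √(64/2) = 3.24. Power is Φ(3.24 − 2.24) = Φ(1.00) = 0.84. Keeping 90% at 0.025 would take 76 per arm, 152 in total, and 152 / 0.80 = 190 after dropout.

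**The case against.** The strongest reply is that multiplicity rules are often left to the analysis plan or full protocol, neither of which is shown, and that a condensed article should not be faulted for silence. That is partly right, since an unseen document may hold a rule. But the article is not simply silent. It states the threshold, the primary measure and the design alpha and power, and those figures mean different things under the two success rules.

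A second reply is that the aim is worded jointly, for pain and balance, and the size was calculated on both outcomes, which fits a both-required design. It does fit, but nothing establishes it, and joint power would then need restating.

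Four stronger readings are tempting, and the documents do not support them:

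- **That 5% control is lost outright.** It is lost only if either outcome suffices, and the article never calls 0.05 a trial-wide rate.
- **That four tests are planned, two outcomes at two visits.** Independence would give 1 − 0.95⁴ = 18.5%, and assumed correlations of 0.5-0.7 between visits and 0-0.5 between outcomes give about 15-17%. The article plans one interaction per outcome and no separate test at each visit. The four-test count is one possible reading, left open because no contrast is fixed.
- **That VAS alone determines the 160, so BBS is safely powered.** This holds only if the 146 already includes dropout, which the Sample size section does not say.
- **That the Discussion sentence on bone loss, falls and fractures is a planned decision rule.** It is worded as a hope and changes no error rate.

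**Conclusion.** The concern stands in conditional form. The article applies one unadjusted 0.05 to two primary outcomes, with no success rule and no fixed primary visit or contrast. The trial-wide error is about 8-10% if either outcome can carry the claim. It is at most 5% if both are required, with joint power of about 81-83% given 90% for each outcome. Except in the limiting case of perfectly correlated tests, neither reading provides both 5% error and 90% power.

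The 9.75% and 81% follow from the stated alpha and power under independence. The other values rest on assumed correlations up to 0.7 for the error rate and 0.5 for joint power. The joint power also assumes that BBS really has 90%, which the article leaves unclear. No error is shown in the 160 as derived from VAS.

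Separately, and as a minor point of wording, the hoped-for recommendation goes beyond the primary outcomes. BMD and fall risk (TUG, MFS) are secondary, fracture is not a listed outcome, and falls enter only as a recent-history item within the MFS.

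**What to change.** Before database lock, state one success rule for VAS and BBS:

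1. **Holm at overall 0.05.** Power for VAS at the stricter step (0.025) falls from 90% to about 84% with 64 evaluable per arm. That is a floor, because VAS is tested at 0.05 if BBS passes its own 0.025 step.
2. **A pre-stated fixed sequence, each test at 0.05.** The first outcome loses no alpha, but the second cannot be claimed if the first fails. The article does not rank the two, so the sponsor must choose the order and give a reason.
3. **Both required, each at 0.05.** No alpha is lost, but the joint power must be restated in place of 90%.

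Apply the rule to one named contrast from the GEE, for example the between-group difference at 6 months. This changes or narrows the group-by-time interaction now called the primary measure, so the two statements must be reconciled and the time coding given. Treat the other visit and the secondary outcomes as supportive.

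State whether the 146 for BBS includes dropout. If it does not, it becomes 183, and BBS does not keep 90% power at 160.

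Limit the confirmatory conclusion to pain and balance. All of this takes a few sentences. The real costs are the power or claim given up under the chosen rule.

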### Study population

The participants are OP patients, with no gender restriction. The diagnostic, inclusion, exclusion, and withdrawal criteria are as follows.Diagnostic criteriaReferring to the *Chinese Guidelines for the Diagnosis and Treatment of Primary Osteoporosis* (2022) [18] and WHO [19], the diagnosis is mainly based on the BMD of dual energy X-ray absorptiometry (DXA). Based on DXA results, the study will select T-value ≤ -2.5 as the subject screening criterion. DXA will be operated by trained imaging technicians assigned by each sub-center.Inclusion criteriaEligible participants meet the following criteria: 1) Primary OP: T-value ≤ -2.5. 2) Female aged from 45 to 70 years old and menopause time is greater than 2 years, which are met at the same time. Male aged from 50 to 70 years old. 3) Visual analogue scale (VAS) is greater than or equal to 3 points. 4) Patients who are willing to participate in the study.Exclusion criteriaThe exclusion criteria are as follows: 1) Lumbar fusion or severe degeneration hinders BMD measurement, and there are less than two continuous intact lumbar vertebrae that can be evaluated by DXA. 2) Patients with serious primary diseases, such as cerebrovascular, digestive tract, and lung diseases, because these clinical manifestations may interfere with the results of the study. 3) Secondary OP: abnormal bone mass caused by similar diseases, including diabetes, thyroid disease, Cushing's syndrome, rheumatoid arthritis, multiple myeloma, gout, malabsorption syndrome, systemic lupus erythematosus, etc. 4) The participants have taken drugs that affect bone metabolism within 3 months before enrollment, such as bisphosphonates, glucocorticoids, calcitonin, anticonvulsant drugs, heparin, etc. 5) Those with a history of severe mental illness or poor compliance. 6) Allergic constitution. 7) Those who have participated in other clinical trials within 3 months.Withdrawal criteria and managementParticipants will be allowed or required to withdraw for the following reasons: 1) Violation of the protocol. 2) Severe illness that prevents continuation. 3) Serious adverse events during the study period. 4) Voluntarily asked to withdraw from the trial. 5) Lost to follow-up. 6) Using drugs that may affect bone metabolism during the period.

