### Recruitment

Participants will be recruited from hospitals or communities in Beijing, Tianjin, and Shaanxi province, China. The recruitment form is mainly a combination of online and offline methods, including Internet publicity, and setting up on-site recruitment stations, etc. First, potentially eligible individuals will complete doctors screening to determine their eligibility based on inclusion and exclusion criteria. Qualified individuals interested in participating in the study will have an informed discussion with trained research assistants. Research assistants will obtain Informed Consent before starting the baseline assessment.

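### The planned GEE allows for correlation within a participant only, so the standard error of the BDJ effect will be understated if outcomes correlate within BDJ training groups

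*Protocol article*

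**What the plan says.** Statistical analysis names the model for primary and secondary outcomes and gives its purpose: "To account for correlation among repeated measurements". The baseline measurement is the covariate, and the group-by-time interaction is the measure of effect. No term for coach, training group or team appears, and Sample size includes no design effect.

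Intervention describes group delivery in the BDJ arm. In the two-week preparatory stage, practice is organised three times a week, and "The researchers will hire professional coaches to guide and correct the movements". In the remaining 22 weeks a research assistant leads one session a month, and participants otherwise practise by themselves. The section adds: "We will recommend the participants form a small team to exercise together with their familiar people". The control arm receives calcium carbonate and D3 only.

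On centres, Recruitment states "Participants will be recruited from hospitals or communities in Beijing, Tianjin, and Shaanxi province, China", and Study population states "DXA will be operated by trained imaging technicians assigned by each sub-center". Randomization is of individuals, "randomly divided into the control group and the treatment group, with 80 patients in each group".

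**The concern.** Two BDJ participants who share a coach, a class or a team may end with outcomes more alike than two participants who share nothing. The document itself gives reasons to expect this. Teams are meant to raise compliance, which the Discussion calls the biggest challenge, and the limitations say the effect may suffer if the movements are not practised correctly. If teammates affect adherence and coaches affect technique, part of the outcome variation lies between groups, in one arm only.

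A GEE whose cluster is the participant handles the repeated visits of one person and treats different people as independent. Robust standard errors at participant level do not repair this. Any positive within-group correlation then biases the result in one direction: intervals for BDJ are too narrow and P values too small. The trial hopes to support a recommendation for practice, so an overstated claim of benefit is the error that matters.

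**Working it through.** **Inputs from the document (Sample size).** Significance level 0.05, power 90% and equal arms. On the resulting number the section says "then the sample size is 64 cases respectively in the two groups, totaling 128 cases according to VAS". Dropout is put at 20%. Sidedness is not stated, and two-sided is assumed.

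**The plan's own figure.** 128 / (1 − 0.20) = 160, which reproduces the stated total. The 64 per arm cannot be rebuilt because the assumed difference and SD are not given. The standardised difference that it implies is d = √(2 × (1.960 + 1.282)² / 64) = 0.573.

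**Assumptions, not in the document.** Group size m and ICC. Clustering is in the BDJ arm only, with 64 evaluable per arm and a normal approximation.

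**Formulas.**
- Design effect in the BDJ arm: DE = 1 + (m − 1) × ICC
- Variance of the difference is multiplied by f = (1 + DE) / 2
- True SE / modelled SE = √f
- Actual type I error = 2 × (1 − Φ(1.960 / √f))
- Power of a test that uses the correct SE = Φ(d / √(2f / 64) − 1.960)
- Enrolment to keep 90% power = 2 × (64f, rounded up) / 0.8

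**Worked case, m = 8, ICC = 0.05.** DE = 1 + 7 × 0.05 = 1.35; f = 1.175; √f = 1.084. Type I error = 2 × (1 − Φ(1.808)) = 0.071. Power = Φ(3.241 / 1.084 − 1.960) = 0.849. Enrolment: 64 × 1.175 = 75.2, so 76 per arm, and 152 / 0.8 = 190.

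| m | ICC | DE | True/modelled SE | Type I error | Power | Enrolled for 90% |
|---|---|---|---|---|---|---|
| 3 | 0.02 | 1.04 | 1.010 | 5.2% | 89.4% | 165 |
| 5 | 0.02 | 1.08 | 1.020 | 5.5% | 88.9% | 168 |
| 8 | 0.05 | 1.35 | 1.084 | 7.1% | 84.9% | 190 |
| 10 | 0.05 | 1.45 | 1.107 | 7.7% | 83.4% | 198 |
| 8 | 0.10 | 1.70 | 1.162 | 9.2% | 79.7% | 218 |
| 10 | 0.10 | 1.90 | 1.204 | 10.4% | 76.8% | 233 |

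A larger class with weaker correlation falls between these cases: m = 20 with ICC 0.01 gives an SE ratio of 1.046 and a type I error of 6.1%.

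**Number of groups.** With 64 evaluable BDJ participants, groups of 8 mean 64 / 8 = 8 groups, and groups of 10 mean about 6. Robust errors over so few groups need a small-sample correction. The table includes none.

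**Centre, checked separately.** With individual randomisation and arms roughly balanced within centre, true SE / modelled SE = √(1 − ICC). For a centre ICC of 0.01, 0.05 and 0.10 this is 0.995, 0.975 and 0.949, with type I error 4.9%, 4.4% and 3.9%. The effect of omitting centre runs the other way.

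**The case against.** The strongest case against is that the document shows little sustained group contact. Regular coached sessions fill 2 of 24 weeks; after that there is one led session a month. Teams are recommended, not required, and the familiar people in them are not said to be trial participants; a team with one trial participant creates no clustering. The Discussion's remark about encouraging residents who know each other is not limited to the BDJ arm. If acquaintances are recruited and then randomised individually, their similarity spans both arms and is not the structure calculated above. For the small teams described, the likely effect is a fraction of a percentage point in type I error.

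All of this stands as an argument for a low to moderate ICC, and it rules out saying that the standard errors are too small as a matter of fact. It does not remove the point. Organised coached sessions are given to one arm only, and the stated model has no place for any correlation that they produce.

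A reader might also infer that running the trial at several sub-centres without a centre term makes the standard errors too small. The calculation shows the reverse under roughly balanced individual randomisation: they are slightly too large. A reader might further infer that randomisation is unstratified and exposed to imbalance between centres. The document does not say so. It leaves number generation to a data management department, and strata and blocks are details that an article may leave to the full protocol.

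**Conclusion.** The point holds conditionally. The stated analysis makes no allowance for correlation between BDJ participants who train together, and any such correlation would understate the standard error of the BDJ effect. The consequence is minor with teams of 3 to 5 and an ICC of 0.02: the true SE is 1 to 2% larger than modelled and type I error is about 5.2 to 5.5%. It is material with groups of 8 to 10 and an ICC of 0.05 to 0.10: 8 to 20% larger, type I error about 7 to 10%, and power between 85% and 77% instead of 90%.

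These figures rest on assumed group sizes and ICCs, a two-sided test, the implied difference of 0.573 SD and non-overlapping groups in the BDJ arm alone. The document cannot show where in this range the trial lies. Centre is no part of this conclusion and enters only as a possible gain in precision.

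**What to change.** - **Record the grouping.** For each BDJ participant, record the organised training group or coach and, where they exist, the other trial participants in the same team. Do this while groups are forming, since membership is hard to reconstruct later. Coach, session group and informal team may cross or change, so name in advance which one defines the cluster; the organised training group is the most stable choice.
- **Pre-specify the analysis.** At least as a sensitivity analysis for VAS and BBS, fit either a mixed model with a training-group random effect in the BDJ arm only, or a GEE clustered on training group with each control as a cluster of one. Use small-sample robust errors with the GEE. Report the estimated ICC.
- **Add centre as a covariate** in the outcome models, for precision.

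The cost is one or two CRF fields and a few model terms. Intervals will be somewhat wider if within-group correlation exists, and power is then below 90% at 160 participants, as the table shows. If there is none, the results should change little.
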